#### Main endpoints

##### Health-related quality of life

In the three RCTs, the difference between the two treatment arms in MHS of the SF-36 will be compared at 12 months using a linear regression analysis, using treatment and the baseline measurement as covariates (analysis of covariance).

##### Disease remission

In the three RCTs, the percentage of patients that achieve disease remission at 36 months will be calculated for the two treatment arms with corresponding 95% confidence interval and compared using a chi-square test.

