### Treatment allocation

Within each RCT (PRolaCT-1, PRolaCT-2, or PRolaCT-3), participants are randomly allocated in a 1:1 ratio to either neurosurgical counselling (with potential subsequent surgery when desired) or standard care with DA. Randomisation is performed in blocks of sizes varying between 4, 6, and 8 patients and is stratified by sex to equally divide male participants and by tumour size (< 10 mm versus ≥ 10 mm). Randomisation is performed centrally in the LUMC using the built-in randomisation tool of the web-based database programme (Castor Electronic Data Capture (EDC), Castor, Amsterdam, the Netherlands). Investigators, treating physicians, and participants will not be blinded to the outcomes of randomization. With the use of varying block sizes, the allocation sequence is kept concealed by the randomisation programme. In PRolaCT-O, treatment choice, based on patient and physician preference, is solely recorded and may be DA treatment as a first- or second-line treatment, or surgical counselling as a second-line treatment (thus not in newly diagnosed patients). For all studies, the interpreters of MRIs, ophthalmologic assessments, and surgical difficulty will be blinded when possible. Unblinding will not occur.

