### Sample size calculation

To detect a difference in remission rate at 36 months of 40% between surgery (expected rate 90%) and medical treatment (expected rate max. 50%), with a power of 0.8 and an *α* of 0.025, 55 patients per treatment group arm are needed, when considering that max. 30% in the interventional arm will not undergo surgery. However, to detect a difference of 10 points at the SF-36 mental health scale at *T* = 12 with an *α* of 0.025 and a power of 0.8, assuming that the standard deviation is 16, based on the general population [31], and that max. 30% of the interventional arm does not undergo surgery, at least 101 patients per treatment arm are needed. To compensate for the loss to follow-up, it is aimed to include 110 patients per treatment arm and therefore 220 patients in total per RCT/PRolaCT-O (aiming for at least 110 patients per treatment group in PRolaCT-O). If patient recruitment would prove challenging, and the required sample size for separate analyses of the RCTs cannot be reached for two or more of the RCTs (PRolaCT-1, PRolaCT-2, or PRolaCT-3) within the duration of the study, the planned analyses could be performed using the combined sample size for two to three RCTs of 220 patients.

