### Planned statistical analyses

We intend to perform all statistical analyses separately for PRolaCT-O and PRolaCT-1, PRolaCT-2, and PRolaCT-3. However, a combined analysis of two to three RCTs may be performed, as stated above, using a regression analysis with adjustment for randomisation group type. A post hoc meta-analysis including all three RCTs and PRolaCT-O will be performed, whatever the course of the study.

To account for positive results due to multiple testing, a lower than usual *p*-value, i.e. < 0.02, will be considered statistically significant. All statistical analyses will be performed according to the intention-to-treat principle. In a sensitivity approach, a per-protocol analysis will also be performed, which may be of added value in case many patients, after consultation, decide not to be operated.

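### Both primary analyses omit the stratification factors sex and tumour size: the tests stay valid but are slightly conservative if these are prognostic, and adding them costs nothing

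*Protocol article*

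**What the plan says.** Treatment allocation: within each RCT "participants are randomly allocated in a 1:1 ratio", in "blocks of sizes varying between 4, 6, and 8 patients", and the randomisation "is stratified by sex to equally divide male participants and by tumour size", with the size cut at 10 mm.

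Main endpoints, Health-related quality of life: the 12-month mental health score (MHS) is compared by linear regression "using treatment and the baseline measurement as covariates (analysis of covariance". Sex and tumour size are not in the model.

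Main endpoints, Disease remission: the percentage in remission is given for each arm with a 95% confidence interval, and the arms are "compared using a chi-square test". No strata enter, and no interval for the difference between arms is mentioned.

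Three other places bear on this:

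- Planned statistical analyses: if RCTs are pooled, the regression adjusts for randomisation group type only.
- The PRolaCT-O section lists gender and prolactinoma size among the potential confounders.
- Statistical analyses of secondary outcomes allows adjustment for prognostic baseline variables for efficiency, and gives risk differences with intervals for dichotomous outcomes.

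No reason is given for leaving the two factors out of the primary analyses.

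**The concern.** Stratified blocks keep the arms balanced on sex and tumour size, so differences in outcome between strata hardly contribute to the real sampling variance of the treatment comparison. An analysis that ignores the strata still counts those differences as noise. If the factors predict outcome, its standard error is too large, its p-values are too large on average, and its type I error falls below the nominal level.

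What is at stake is some power. The MHS sets the sample size, the significance threshold is strict, and the Discussion (Strong patient preference) reports limited recruitment so far. The article names both tests and the ANCOVA covariates, so this is a stated analysis choice and not a detail left open.

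**Working it through.** **1. The plan's own sample sizes.** Inputs from Sample size calculation: remission 90% versus 50%; a 10-point MHS difference; SD 16; up to 30% of the intervention arm not operated; "with a power of 0.8 and an *α* of 0.025". Sidedness is not stated; two-sided reproduces the figures.

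- Diluted remission rate: 0.7 × 90% + 0.3 × 50% = 78%, a difference from 50% of 28 points. With pooled rate 0.64, n = [2.241 × √(2 × 0.64 × 0.36) + 0.842 × √(0.78 × 0.22 + 0.50 × 0.50)]² / 0.28² = 54.6, so 55 per arm, as stated.
- Diluted MHS effect: 0.7 × 10 = 7 points. n = 2 × (2.241 + 0.842)² × 16² / 7² = 99.3, so 100; the t-test version gives 100.6, so 101, as stated.

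**2. MHS: effect of omitting the strata.** Let R² be the share of residual variance, after baseline MHS, that the strata explain. The article gives no value, so 0 to 0.10 is assumed. As in the plan's own calculation, SD 16 is used with no credit for baseline. The threshold is the one for analysis: "a lower than usual *p*-value, i.e. < 0.02, will be considered statistically significant", so z = 2.326. At 101 per arm, SE = 16 × √(2/101) = 2.252 and 7/2.252 = 3.109.

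Under stratified allocation the true standard error is SE × √(1 − R²), whichever analysis is used. The unadjusted analysis reports SE; the adjusted one reports the true value. Hence:

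- Type I error, unadjusted: 2 × [1 − Φ(2.326/√(1 − R²))]
- Power, unadjusted: Φ[(3.109 − 2.326)/√(1 − R²)]
- Power, adjusted: Φ[3.109/√(1 − R²) − 2.326]

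| R² (assumed) | Type I error, unadjusted | Power, unadjusted | Power, adjusted | Gain (points) |
|---|---|---|---|---|
| 0 | 2.0% | 78.3% | 78.3% | 0 |
| 0.02 | 1.9% | 78.5% | 79.2% | 0.7 |
| 0.05 | 1.7% | 78.9% | 80.6% | 1.7 |
| 0.10 | 1.4% | 79.5% | 82.9% | 3.4 |

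Unadjusted power rises with R² because the stratified design helps that analysis too. Setting 78.3% against every adjusted figure would overstate the gain. That 78.3% falls below 80% because the threshold is 0.02 while the sample size used 0.025 (at 0.025 it is 80.7%). This is a separate matter from stratification.

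**3. Remission: chi-square against stratified Mantel-Haenszel (MH).** Trials were simulated with equal allocation within strata.

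*Two strata by tumour size.* Assumed: control remission 60% and 30%, a 70/30 split, the planned 28-point difference, threshold 0.02.

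| Per arm | Power, chi-square | Power, MH |
|---|---|---|
| 55 | 80.5% | 82.9% |
| 101 | 98.0% | 98.5% |
| 110 | 98.7% | 99.1% |

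In this scenario the chi-square type I error is about 1.4 to 1.6%, against about 2.0% for MH.

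*Four strata.* Stratum shares of 65/10/15/10% are assumed, consistent with the Background's 80% microprolactinomas and three women to one man. The odds ratio (OR) per factor is assumed, rates are 78% versus 50%, and α is 0.025.

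| OR per factor | Type I error at 110 per arm, chi-square / MH | Power at 110, chi-square / MH | Power at 55, chi-square / MH |
|---|---|---|---|
| 1 | 2.6% / 2.6% | 98.7% / 98.6% | 80.6% / 80.4% |
| 2 | 2.3% / 2.5% | 98.8% / 98.9% | 81.6% / 82.0% |
| 3 | 1.9% / 2.5% | 99.1% / 99.3% | 83.2% / 85.3% |
| 5 | 1.4% / 2.5% | 99.4% / 99.7% | 85.0% / 89.4% |

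The chi-square statistic is discrete, so its error rate moves by a few tenths of a point with n even when the factors are not prognostic (2.8% at 101 per arm with OR 1). That has nothing to do with the strata.

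**The case against.** The strongest reply is that nothing here is invalid. An unstratified test after stratified randomisation errs on the safe side, the gain depends on a prognostic strength that the article does not give, and baseline MHS already absorbs part of any sex or size effect. If baseline and 12-month MHS correlate at 0.5 (assumed), power at 101 per arm and α 0.025 is already 91.1%, which leaves less to gain. All of this stands, and it limits the point to efficiency.

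Three stronger readings are tempting, and the article does not support them.

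- **Remission suffers most, because it plausibly depends on tumour size.** Not at the planned effect and size. The MHS sets the numbers, so remission has power near 98% in reserve. A visible loss at 101 per arm needs a difference well below the planned diluted 28 points, and the article plans for no such effect.
- **The sample sizes or the error control are wrong.** Both stated sample sizes reproduce, and ignoring prognostic strata lowers the type I error.
- **The pooled analysis ignores the trial.** Planned statistical analyses adjusts it for randomisation group type, most naturally read as which RCT. Only sex and tumour size are absent.

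The lack of an interval for the remission difference is a reporting matter, separate from stratification. It is mentioned only because the same change settles it.

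**Conclusion.** The point holds as a modest efficiency improvement. Both primary analyses leave out factors used in the randomisation. If those factors are prognostic, the tests are conservative and lose a little power; if not, nothing is lost.

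For the MHS at 101 per arm and threshold 0.02, the gain from adjusting is 0 to 3.4 points for assumed R² of 0 to 0.10. At R² 0.05 it takes power from 78.9% to 80.6%. For remission at 78% versus 50%, it is about 0.5 points or less at 101 to 110 per arm. It reaches about 2 to 3 points only if numbers fall to around 55 per arm with moderately prognostic strata, and more only under strong ones (OR 5 per factor).

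The facts and the direction are certain. The size rests on the assumed prognostic strength, the assumed stratum mix and, for the MHS, a normal approximation with SD 16.

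**What to change.** - **MHS:** add sex and tumour-size stratum to the ANCOVA beside treatment and baseline MHS.
- **Remission:** replace the plain chi-square by a Mantel-Haenszel test stratified by sex and tumour size. Report a stratified or standardised risk difference with its confidence interval; the per-arm percentages can stay.
- **Pooled RCT regression:** add sex and tumour size to the existing adjustment for trial.

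Both factors are recorded at randomisation, so the cost is analysis wording only: no new data and no change in sample size. The change should be fixed before outcome data by arm are seen.

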##### Analyses in PRolaCT-O using propensity score methods

As the treatment groups in PRolaCT-O may differ at baseline, propensity score methods will be used to account for potential confounding. The propensity to receive surgical counselling will be estimated using logistic regression including potential confounders such as duration and effectiveness of prior DA treatment, the amount and severity of side effects to DA treatment measured at study entrance measured with the PRO-CTCAE, age at inclusion, gender (male or female), type of centre treatment takes place (secondary or tertiary), physician enrolling the patient (endocrinologist, gynaecologist, or neurosurgeon), prolactinoma size (micro- or macroadenoma), patient and MDT treatment preference pre- and post-counselling (neutral, medication, or surgery), and the likelihood of positive surgical outcome (unlikely, possibly, or likely) as estimated post hoc by two neurosurgeons blinded to received treatment. Adequacy of the propensity model will be assessed by checking if standardised mean differences after propensity adjustment are below 0.10 and by inspecting balancing plots.

Inverse probability weighting based on the propensity score will be used to balance the treatment groups. After observations are reweighted, treatment groups are compared in the same way as in the RCTs. Propensity matching will be used as a sensitivity analysis.

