## Methods

### Study design

This combined randomised clinical trial and observational cohort study design comprises three unblinded parallel superiority prolactinoma RCTs (PRolaCT-1, PRolaCT-2, PRolaCT-3) and an observational study arm (PRolaCT-O) that will compare counselling for endoscopic transsphenoidal adenoma resection to standard care (DA treatment) in patients with a prolactinoma of limited size (i.e. < 25 mm, no tissue invasion):
PRolaCT-1 compares counselling for surgical resection as a first-line treatment in newly diagnosed, treatment-naïve prolactinoma patients.PRolaCT-2 compares counselling for surgical resection as an early second-line treatment in patients who have had DA treatment for a limited time period (4–6 months).PRolaCT-3 compares counselling for surgical resection as an equal second-line treatment in patients who have persisting prolactinoma, i.e. recurring hyperprolactinaemia and persisting pituitary adenoma on MRI, after DA treatment for a long period of time (> 2 years).PRolaCT-O evaluates counselling for surgical resection as an equally valid second-line treatment and standard care in an observational study setting, aiming to include all patients eligible for PRolaCT-1, PRolaCT-2, and PRolaCT-3 who do not participate in the RCTs because of a strong patient and/or physician treatment preference, and/or because the patient does not consent to randomisation.

All interventions and study procedures are otherwise identical for the three RCTs and the observational cohort.

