#### Study setting

Endoscopic surgery is centralised in a few tertiary expert neurosurgical centres, while endocrine care for prolactinoma is delivered by endocrinologists and gynaecologists in all hospitals. For an expected enrolment period of 3 years, starting June 2019, recruitment for PRolaCT operates from five participating neurosurgical reference centres and uses regional multidisciplinary networks to recruit patients from the referring hospitals. PRolaCT is furthermore intended to expand to other reference centres in the Netherlands and internationally to the UK, France, and Germany, in collaboration with European Networks.

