### Treatment

#### Intervention: surgical counselling

Participants who are randomised for the intervention group will receive extensive and personalised neurosurgical counselling by a neurosurgeon and an endocrinologist with specific expertise in pituitary care (preferably a combined consultation). All potential benefits and risks of surgery are discussed in a semi-standardised manner, offering both standardised information on surgical intervention and detailed expert opinion regarding the patient’s specific situation. This consultation may theoretically result in advising the patient to refrain from surgery during the shared decision-making process, despite the patient’s previous eligibility “on paper”. Moreover, based on information gathered during the counselling, the MDT may advise against surgery and propose standard treatment as a better alternative in this individualised approach. After counselling, the patient is asked for consent for surgery as is a standard preoperative requirement regardless of study participation. Participants in the intervention group may thus decide not to proceed with the surgical intervention. Participants who do not consent to surgery will continue the RCT in the intervention group, but receive treatment according to standard care. Patients receiving standard of care may be referred back to their own physician following the counselling.

When a participant and the MDT agree to surgery, an endoscopic transsphenoidal surgical resection of the prolactinoma is performed according to standard practice in an expertise centre. Patients are hospitalised for 2–5 days postoperatively. In the first weeks after discharge from the hospital, frequent contact by phone or visits to the outpatient clinic are needed to check for complications and recovery of the patient, according to the standards of care of the neurosurgical centre. The frequency of these visits is gradually reduced to (half-)yearly visits depending on the patient’s well-being.

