### Outcome assessment

Assessment of clinical outcomes takes place during outpatient clinic visits at 12, 27, 36, and 60 months after randomisation (PRolaCT-1, PRolaCT-2, and PRolaCT-3), or after study baseline (PRolaCT-O). For PRolaCT-O, study baseline is defined as the moment randomisation would have taken place, thus after all baseline measurements are performed and when treatment is chosen. An extensive overview of enrolment, interventions, and outcome assessment is given in Table 1. During these visits to the outpatient clinic, registration of prolactinoma treatment, physical symptoms, pregnancy, laboratory measurements (including prolactin level), and pituitary MRI (only at 12 and 36 months) takes place. For all surgically treated patients, the final registration of complications takes place during the outpatient clinic visit at 12 months. At every time point, assessment of patient-reported outcome measurements (PROMs) will take place using self-reported questionnaires. These questionnaires assess HRQoL and the presence and burden of physical and psychiatric symptoms or side effects to treatment. In all PRolaCT study arms, PROMs will additionally be collected every 3–6 months after randomisation/study baseline until *T* = 36 for a cost-effectiveness analysis.

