## Discussion

### Rationale for the study design

Prolonged DA treatment for prolactinoma, which is current standard practice [1, 4, 5], is very effective in controlling hyperprolactinaemia and restoring gonadal function. However, patients may suffer from substantial side effects compromising HRQoL to a greater extent than previously described, while remission rates following DA treatment are lower than previously thought [5–13, 18–22, 37]. Although there is a low risk of complications, surgical resection induces swift disease remission in most patients, which may allow a drug-free future [5, 17, 23–26, 28, 38–46] with improved or even normalised HRQoL, and may thus deserve a more prominent place in the treatment of prolactinoma patients. However, loss of pituitary function and life-threatening complications must be considered.

The PRolaCT studies combine three randomised clinical trials and an observational cohort and are designed to compare both treatment strategies for patient-relevant outcomes, such as disease remission and HRQoL. For the RCT parts of PRolaCT, patients consent to randomisation between surgical counselling or standard care. If we would randomise between surgery versus DA treatment, all patients would have had to be referred to a neurosurgical expertise centre for surgical counselling prior to entering the study. With our pragmatic RCT design, only patients who randomise for surgical counselling are referred to the regional MDT to receive detailed information about surgical treatment for prolactinoma and standard care is delivered in the regional hospital. Patients who randomise for standard care are thus not burdened with referral to a neurosurgical expertise centre and neurosurgical counselling. Although a greater appeal on regional networks is made, the pragmatic design of PRolaCT intends to lower the threshold for randomisation.

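### In PRolaCT-O the propensity model adjusts for the centre where treatment takes place, which as worded follows from the treatment choice; it should be the centre before counselling

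*Protocol article*

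**What the plan says.** All places are in the protocol article.

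- *Analyses in PRolaCT-O using propensity score methods*: logistic regression models the propensity to receive surgical counselling. The potential confounders include "type of centre treatment takes place (secondary or tertiary), physician enrolling the patient (endocrinologist, gynaecologist, or neurosurgeon". Inverse probability weighting follows, with standardised mean differences below 0.10 and balancing plots as checks and matching as a sensitivity analysis. The target population of the weights is not named.
- *Study setting*: "Endoscopic surgery is centralised in a few tertiary expert neurosurgical centres", whereas "endocrine care for prolactinoma is delivered by endocrinologists and gynaecologists in all hospitals".
- *Intervention: surgical counselling*: once surgery is agreed, "an endoscopic transsphenoidal surgical resection of the prolactinoma is performed according to standard practice in an expertise centre". For those not operated, "Patients receiving standard of care may be referred back to their own physician following the counselling".
- *Rationale for the study design*, on the RCTs: "standard care is delivered in the regional hospital". *Study design* adds: "All interventions and study procedures are otherwise identical for the three RCTs and the observational cohort".
- *Outcome assessment* places PRolaCT-O baseline at the moment randomisation would have occurred, "thus after all baseline measurements are performed and when treatment is chosen".

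**The concern.** A propensity model should contain variables fixed before the exposure. Read literally, the centre where treatment takes place is settled by the choice being modelled: a patient who chooses surgery is treated in a tertiary centre, and a counselled patient who declines may go back to a secondary one. Placing baseline at the time of treatment choice does not prevent this, because the treating centre is then already known.

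Balancing the groups on such a variable compares counselled and DA patients within strata defined partly by the result of counselling. What is at stake is the PRolaCT-O estimate of both primary outcomes. *Study design* makes this cohort a fall-back for the primary objectives, *Strong patient preference* expects it to report before the RCTs, and *Combining the results of the different trials* puts its estimate into the meta-analysis.

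**Working it through.** **1. The plan's own figures.** *Sample size calculation* gives remission of 90% with surgery and at most 50% with medical treatment, up to 30% of the intervention arm unoperated, a 10-point effect on the SF-36 mental health scale (MHS) with SD 16, alpha 0.025 and power 0.80.

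- Diluted remission: 0.7 × 0.90 + 0.3 × 0.50 = 0.78, against 0.50. With mean proportion 0.64 and alpha two-sided, n = [2.241 × √(2 × 0.64 × 0.36) + 0.842 × √(0.78 × 0.22 + 0.50 × 0.50)]² / 0.28² = 54.6, i.e. 55 per arm, as stated.
- Diluted MHS effect: 0.7 × 10 = 7. The normal formula gives 100 per arm; the t-test version gives 100.6, i.e. 101, as stated.

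So the plan treats an unoperated counselled patient as having the medical-treatment outcome. The same rule is used below.

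**2. Model for the covariate.** Assumptions that the documents do not give: 110 patients per group (the plan's minimum aim), centre type as the only covariate, whole-cohort weights (1/propensity), operated share 1−u, share f of the unoperated sent back to secondary care, and share s of DA patients in secondary care.

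- P(sec) = (110·u·f + 110·s) / 220
- Weighted unoperated share = P(sec) + [1 − P(sec)] × (unoperated tertiary) / (all counselled tertiary)
- Remission difference = 40 points × weighted operated share

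**3. One worked case** (u = 0.20, f = 0.5, s = 0.70). There are 88 operated patients, 11 unoperated tertiary and 11 unoperated secondary; the DA group splits 77 secondary and 33 tertiary.

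- Secondary stratum: 11 + 77 = 88 of 220 (40%). Weight per counselled patient: 88/11 = 8.
- Tertiary stratum: 99 + 33 = 132. Weight: 132/99 = 1.33.
- Weighted operated share: 0.60 × 88/99 = 0.533, against a true 0.80.
- Counselled remission: 0.533 × 0.9 + 0.467 × 0.5 = 0.713, against 0.82.
- Difference: 21 points instead of 32.
- Effective size of the counselled group: 220² / (11 × 8² + 99 × 1.33²) = 55 instead of 110.

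**4. Range.** Over 70-90% operated, s = 50-90% and f = half or all:

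| Operated | Sent back | DA in secondary care | Remission difference, true → weighted | Loss |
|---|---|---|---|---|
| 70% | all | 50% | 28.0 → 24.0 | 4.0 |
| 70% | half | 90% | 28.0 → 15.6 | 12.4 |
| 80% | half | 70% | 32.0 → 21.3 | 10.7 |
| 90% | half | 90% | 36.0 → 19.9 | 16.1 |

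The first and last rows are the extremes. The direction is the same throughout.

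**5. Effect on power at the plan's 30% unoperated, all sent back.** For s = 50%, 70% and 90%, the MHS difference is 6, 5 and 4 points instead of 7. Power at 110 per group and alpha 0.025 is 71%, 53% and 35% instead of 84%. For remission it is 93%, 79% and 57% instead of 98.5%. These figures carry no penalty for unequal weights, so they are optimistic.

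**6. If no counselled patient is coded secondary.** With s = 70%, the 33 tertiary DA patients get weight 143/33 = 4.33 and the 77 secondary ones weight 1. The weighted DA group is then 77/220 = 35% secondary against 0% of the counselled group. The standardised difference is 0.35 / √(0.35 × 0.65 / 2), about 1.0, against a target of 0.10.

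**7. If the weights target the counselled group.** Counselled patients keep weight 1, so the dilution in step 3 does not occur. In the same case, secondary DA patients get weight 11/77 = 0.14 and tertiary ones 99/33 = 3. The 33 tertiary DA patients then make up 99/110 = 90% of the weighted comparison group.

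**The case against.** The strongest reply is that the phrase need not mean the post-choice centre. The propensity section is about groups that may differ at baseline, and *Strong patient preference* relies on baseline measurements. *Treatment allocation* limits surgical counselling in PRolaCT-O to second-line treatment, so every counselled patient already had a hospital giving DA care. If that hospital is meant, the covariate is a legitimate confounder and the problem disappears. This stands as a possible reading, but the words name where treatment takes place and nothing ties them to the time before counselling.

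Second, the stratum argument depends on coding. *Safety reporting* mentions intervention patients being referred back to their own hospital without limiting this to the unoperated, so an operated patient may have later care in a secondary centre. How care in two settings is coded is not stated. This is why the point is conditional on coding by where the chosen treatment is given.

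Third, the planned balance checks would expose an empty stratum. That is correct for step 6, but they would not reveal the dilution in step 3, where centre type is balanced by construction.

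A reader might infer two stronger points that the documents do not support. One is that the weighted analysis is certainly biased towards zero: the shares, the target of the weights and the influence of the other covariates are all unknown, and cohort members with firm preferences may seldom forgo surgery after counselling. The other is that the enrolling-physician covariate has the same fault: enrolment can precede counselling, the section does not say the variable is recorded afterwards, and removing the neurosurgeon category could discard a real predictor of counselling.

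**Conclusion.** The point holds on the literal wording. As written, the propensity model includes a variable that results from the treatment choice. Coded that way, it either dilutes the counselled group with upweighted unoperated patients, leaves a stratum without counselled patients, or, with weights targeting the counselled group, shifts the DA comparison towards tertiary DA patients. The loss of about 4 to 16 points in the remission difference rests on whole-cohort weights, centre type as the only covariate, the assumed ranges for the three shares, and the plan's 90% and 50% remission rates. It shows what the wording could do and is not a forecast. The randomised comparisons are not affected. Because PRolaCT-O is the fall-back for the primary objectives, the wording should be corrected before its analysis.

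**What to change.** Define the covariate as the type of centre (secondary or tertiary) treating or referring the patient before any neurosurgical counselling. Report the centre where treatment was actually given descriptively, by group, and keep it out of the propensity model. Leave the enrolling-physician covariate unchanged.

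This keeps the case-mix adjustment that centre type was presumably meant to provide. With no other confounding, the counselled group then keeps its real operated share: at the plan's 30% unoperated, the contrasts stay at 28 points for remission and 7 points on the MHS. The cost is a change of wording and a check that the pre-counselling hospital is recorded at entry for every PRolaCT-O patient.
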